### Aspirin intervention

Those women who assess as high risk (risk ratio ≥ 1/100) will be prescribed aspirin for preeclampsia prevention. The dosage is 100 mg daily begins at 12–16 gestation week. Those women of low risk (risk ratio < 1/100) will not been prescribed aspirin. All the recruited women will be followed up monthly.

### Followup

At monthly antenatal visit, those women will be asked to take their left aspirin pills to the hospital. The clinician will record their compliance through pill counting. All women, regardless of high risk or low risk, will be recorded of blood pressure and newly-onset complications. At 24–24^+6^, 30–36^+6^ gestational week, maternal serum will be stored for the measurement of PlGF and soluble fms-like tyrosine kinase 1 (sFlt-1).

### Endpoint outcomes

Endpoint outcomes are collected at delivery and till 42 days postpartum. Pregnancy outcomes will be recorded include the incidence of preeclampsia, eclampsia, HELLP syndrome (hemolysis, elevated liver enzymes and low platelet), preterm birth, fetal growth restriction/small for gestational age, postpartum hemorrhage, placental abruption, maternal heart failure, pulmonary edema, fetal demise, fetal death, neonatal death, neonatal asphyxia, neonatal intensive care unit (NICU).

### Control and contamination

#### Traditional preeclampsia prevention

Prior to implementation of the Bayes-theorem based preeclampsia risk prediction in each of the eighteen sectors, usual antenatal care for addressing maternal preeclampsia risk evaluation during pregnancy will be provided. Such care is likely to vary by antenatal service and clinician as several guidelines available are varied.

#### Potential for contamination

As PlGF measurement is not available in all eighteen sectors till the initiation of intervention, the Bayes-theorem based preeclampsia risk preventive strategy will not be accessible to clinicians during the baseline phase.

### Measures

#### Primary outcomes

The primary outcomes for this trial is the incidence of preeclampsia. The diagnosis will be collected during pregnancy period, at delivery and till 42 days postpartum, including the detailed onset time and severity. Related complications will also be recorded such as eclampsia and HELLP syndrome.

#### Secondary outcomes

There are obstetric, maternal, fetus/neonatal secondary outcomes for this trial, including the incidence of obstetric complications (preterm birth, placental abruption, postpartum hemorrhage), maternal complications (maternal heart failure, pulmonary edema), fetal complications (fetal growth restriction, small for gestational age, fetal demise, fetal death, neonatal death, neonatal asphyxia, NICU).

### Data collection procedures

#### Primary and secondary outcomes measures

Pregnancy outcomes will be recorded extracted from electronic medical records at delivery and postpartum outpatient visit. Experienced interviewers will confirm these information by telephone at 42 days in postpartum period. The postpartum survey will be pilot tested prior to starting the study to test comprehension, length and logic flow.

#### Process evaluation

At enrollment, women who attend their first antenatal visit before 13^+6^ weeks will be invited to participate in this study and sign an informed consent. Each weekday a sample of women who complete preeclampsia prediction test will be notified about their risk classification. Those women who are at high risk of preeclampsia predicted by the Bayes-theorem based risk model will be telephoned to book a visit for their obstetricians for aspirin prescription, while those women at low risk will be messaged about their results. In the follow-up period, all enrolled women will be contacted for a face-to-face interview for their obstetric complication and blood pressure measurement at their regular antenatal visit. Each weekday a sample of women who are at their 20–24^+5^ and 30–36^+6^ weeks for blood sample collection for PlGF and sFlt-1 measurement.

#### Data management

Data management protocol has been drafted and approved by advisory group of this trial. The whole process of data management will obey this protocol, and collected data will be stored according to the requirement of the Research Ethics Committee of Obstetrics and Gynecology Hospital of Fudan University. Data is accessible to principle investigator and statisticians.

#### Sample size

It is expected that 15,000 eligible pregnant women in all eighteen sectors will register at antenatal visit in first trimester (based on previous annual delivery number in each sector) during the first 18-month enrollment period of this trial. Assuming 70% of invited women will agree to participate in this project, approximately 10,500 women will be enrolled in this study.

### Statistical analysis

Statistical analyses will be conducted on an intention-to-treat basis. Primary and secondary outcomes will be analyzed using a logistic mixed model to determine the significance of the between group difference in the incidence of preeclampsia and other complications, with adjustment for the effect of the estimated risk of preeclampsia at screening and the participating center. Prespecified analyses will be performed in subgroups that were categorized according to the estimated risk of preterm preeclampsia and history of preeclampsia, and a post hoc subgroup analysis according to the participating centers. A sensitivity analysis will be performed to take into account the effect of withdrawal of consent and loss to follow-up. Kaplan–Meier estimates of the cumulative incidence of preeclampsia according to trial group will be conducted, in which deliveries that were not with preeclampsia were excluded. The statistical software package R was used for data analyses.

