## Methods/design

### Study design and setting

The study will be a randomized stepped-wedge controlled trial design conducted in eighteen hospitals in mainland China. The hospitals are geographically defined groupings of antenatal facilities with common obstetric management. As shown in Fig. 1, repeated cross-sectional outcomes data will be gathered on a monthly basis across all eighteen hospitals for the duration of the study (28 months). Baseline data will be collected for each hospital from prior to the commencement of the preeclampsia risk prediction in the first hospital to the start of the intervention in each sector. Stepped implementation of a 2-month practice change of preeclampsia risk prediction will be delivered in a randomly selected order at two monthly intervals. Follow-up data will continue to be collected for all eighteen hospitals following completion of the practice change intervention. The outcomes of the trial will be determined by comparing the incidence of preeclampsia outcomes between the baseline and follow up periods for the eighteen sectors combined.

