**Fig. 1 Fig1:**
[figure not shown]
Preeclampsia risk prediction model for Chinese pregnant women (ChiPERM) stepped-wedge design

A randomized stepped-wedge controlled trial design is recommended for the evaluation of clinical practice change interventions as it provides a number of pragmatic and scientific advantages over a randomized controlled trial design [17, 18]. First, it provides a similar level of evidence as a standard parallel cluster randomized controlled trial. Second, although all the participated hospitals will receive the intervention, its sequential implementation across eighteen sectors provides the capacity to identify secular trends, i.e. changes over time before the intervention is implemented. Third, the design provides an opportunity for all participating services and women to receive the intervention, overcoming ethical and logistical challenges arising from withholding the intervention.

All eighteen hospitals have covered 15 provinces across mainland China. The antenatal services in the eighteen hospitals service urban and rural areas and provide care to over 100,000 women annually, accounting for approximately 1% of births in mainland China.

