### Random allocation and blinding

A statistician who is independent of intervention development and implementation will randomly allocate the order in which the Bayes-theorem based preeclampsia risk prediction is implemented across the eighteen hospitals. The random sequence will be generated using a computerized random number generator with allocation undertaken for all eighteen hospitals at the one time. Study personnel involved in collecting outcome data will be blind to the allocated order of the delivery of the preeclampsia risk prediction across the hospitals. Participants providing outcome data will be informed the experimental nature of preeclampsia risk prediction across hospitals and therefore will not be blind to the stage of study occurring in the service they attend. Given the practice change nature of the preeclampsia risk prediction, clinicians in antenatal services will be aware when their service is in the intervention period.

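### With participating center as the only cluster term named, the primary model ignores hospital-specific drift over time, so its standard error can be too small and its false-positive rate can exceed 5%

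*Protocol article*

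**What the plan says.** Under Study design and setting: "The study will be a randomized stepped-wedge controlled trial design conducted in eighteen hospitals in mainland China". The change in practice "will be delivered in a randomly selected order at two monthly intervals", and "repeated cross-sectional outcomes data will be gathered on a monthly basis across all eighteen hospitals for the duration of the study (28 months"). Under Random allocation and blinding, an independent statistician "will randomly allocate the order in which the Bayes-theorem based preeclampsia risk prediction is implemented across the eighteen hospitals". The randomised unit is therefore a hospital's place in the rollout, and each hospital contributes separate groups of women in successive periods.

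Under Statistical analysis: "Primary and secondary outcomes will be analyzed using a logistic mixed model to determine the significance of the between group difference in the incidence of" each listed event. The terms of that model are then given: "with adjustment for the effect of the estimated risk of preeclampsia at screening and the participating center". No calendar-period term, hospital-by-period term, decaying correlation, robust variance or small-sample correction is named. The section does not say whether center is random or fixed.

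Two other places bear on drift. The text below Figure 1 gives as a merit of the design that it "provides the capacity to identify secular trends, i.e. changes over time before the intervention is implemented". Of usual care before the switch, the section on traditional prevention says: "Such care is likely to vary by antenatal service and clinician as several guidelines available are varied".

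**The concern.** The listed terms suit a multicentre trial that randomises individual women, where center only has to absorb constant differences between sites. In a stepped wedge each hospital is largely compared with itself before and after its switch, so what counts as noise is how much a hospital's own rate wanders between periods. A center term alone sets that wandering to zero: two women in one hospital are as alike a year apart as in the same month. Changes in staff, diagnostic habit or local usual care are then treated as binomial sampling error.

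A fixed period effect does not cure this. It removes drift shared by all hospitals, not drift peculiar to one. At stake are intervals that are too narrow and p-values that are too small, for the primary outcome and every secondary outcome analysed the same way.

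**Working it through.** **The plan's own figure.** The Sample size section expects 15,000 eligible women and 70% participation: 15,000 × 0.70 = 10,500, as stated. This is a recruitment forecast. No alpha, power, effect size, ICC or between-period correlation is given, so what follows rests on assumptions.

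**Assumptions.** 18 hospitals (stated); 2-month periods (stated step length); 9 sequences of 2 hospitals over 10 periods (assumed, since Figure 1 is not available); incidence p = 4%, within the 2–8% in the Background; two-sided 5% test; no treatment effect; fixed period effects already in the model. Women per hospital-period: 10,500 / (18 × 10) ≈ 58.

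**Formula.**
- Total hospital variance on the log scale: σ² = ln(1 + ICC(1−p)/p). For ICC 0.01 this is ln(1.24) = 0.215; for ICC 0.05 it is ln(2.2) = 0.788.
- Let r be the between-period correlation divided by the within-period correlation. The variance that a center term misses is τ² = σ²(1−r).
- Binomial variance of a cell's log-odds: 1/(m·p(1−p)), with m·p(1−p) = 58 × 0.04 × 0.96 = 2.227.
- With center as a fixed factor and equal cells, true SE / model SE = √(1 + 2.227 τ²). This does not depend on the number of sequences.
- False-positive rate = 2(1 − Φ(1.96/ratio)).

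| ICC | r | τ² | SE ratio | Rate, center fixed | Rate, center random | Two simulations |
|---|---|---|---|---|---|---|
| any | 1 | 0 | 1.000 | 5.0% | 5.0% | about 5% |
| 0.01 | 0.8 | 0.043 | 1.047 | 6.1% | 5.8% | 5.9%, 6.7% |
| 0.01 | 0.5 | 0.108 | 1.113 | 7.8% | 6.9% | 7.4%, 8.7% |
| 0.05 | 0.8 | 0.158 | 1.162 | 9.2% | 8.9% | 11.1%, 13% |
| 0.05 | 0.5 | 0.394 | 1.370 | 15.3% | 14.7% | 17.8%, 23% |

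The random-center column is a sandwich calculation for the same layout. Each simulation used 1,500 replicates.

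**Other layout and incidences.** Take 6 sequences of 3 hospitals over nine 2-month periods, about 65 women per hospital-period, with the ICC on the latent logit scale (latent 0.05 is about 0.008 as a proportion at 4%).
- 4% incidence, latent ICC 0.05: 5.9% (simulated 6.7%) at r = 0.8 and 7.3% (7.5%) at r = 0.5.
- 4% incidence, latent ICC 0.10, r = 0.5: 10.0% (11.8%).
- Latent ICC 0.05, r = 0.8: 5.5% (5.1%) at 2% incidence and 6.8% (6.4%) at 8%.
- Worst case examined, 8% incidence, latent ICC 0.10, r = 0.5: 14.7% (16.6%).

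**How plausible is each ICC?** With hospital rates log-normal around a mean of 4%, ICC 0.01 implies a 95% range of about 1.4–8.9%, and ICC 0.05 about 0.5–15%. The Background's 2–8% describes pregnancies in general, so it is only a rough check, but it makes 0.05 look extreme.

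**The missing period term, for scale.** With no time term, r = 1, latent ICC 0.05 and 4% incidence, the rate is 5.2% without a trend. It is 8.4%, 19.1% and 38.9% if the odds fall by 10%, 20% and 30% over enrolment.

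**Does the remedy work?** In the 6-sequence layout at 4% (400 runs, Monte Carlo error about 1 to 1.4 points), a random hospital-by-period intercept gave:
- latent ICC 0.05, r = 0.8: 7.0% with a z test, 4.3% with t on 16 df (center only, z: 6.7%);
- latent ICC 0.10, r = 0.5: 8.0% with z, 5.0% with t on 16 df (center only, z: 11.8%).

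Permuting the hospital order (600 replicates, ICC 0.05, r = 0.8) gave 5.3% at 58 women per cell.

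**The case against.** The best reply is that a condensed article need not write out its random effects, and that a fuller plan may add a period term, a hospital-by-period term and a small-sample correction. That stands as a caution. But the section is not silent: it names the model and its adjustment terms, and those terms fit a different design.

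Second, the excess is conditional. It needs both a non-trivial ICC and decay of the correlation, and the article states neither. This stands and is built into the point. Adjustment for each woman's screening risk would also absorb some drift in case mix, which the calculations leave out.

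Third, a reader might take the over 100,000 women a year described for these hospitals as the analysis set. That is about 100,000 / (18 × 6) ≈ 926 women per hospital-period, and simulated rates at r = 0.8 reach 24% (ICC 0.01) and 48% (ICC 0.05). The documents do not support this reading: that figure describes service volume, consent is an inclusion criterion, and the Sample size section plans about 10,500 women. Likewise, 28 months is the data-collection span, whereas enrolment is planned over 18 months, so the correlation has less time to decay than 28 months suggests.

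**Conclusion.** The point holds in conditional form. The only cluster term named assumes a constant within-hospital correlation over time. If hospital rates drift independently, the standard error can be too small and the false-positive rate can exceed 5%, even with period effects added. A reader might infer that the rate must exceed 5%; the documents do not show that, because with no decay it is exactly 5%.

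At the planned size the excess is modest in plausible settings (about 1 to 4 points at proportion-scale ICC 0.01) and becomes large only at an ICC of 0.05, which implies an improbable spread of hospital rates. All of this rests on the assumed 4% incidence, ICC, decay and layout. The missing calendar-period term is the larger defect in that sentence, but repairing it alone leaves this one. The model should be changed before outcomes are seen; the point does not undermine the design.

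**What to change.** In the Statistical analysis section, specify a logistic mixed model with fixed 2-month period effects, a random hospital intercept and a random hospital-by-period intercept, tested against a small-sample reference distribution for 18 clusters (for example t on about 16 df). Alternatively, take the primary p-value from a permutation test that re-randomises the order of the 18 hospitals as in the allocation. The hospital-by-period term should not be added with an ordinary z test: with 58 × 0.04 ≈ 2.3 events per cell its variance is poorly estimated, and it left 7–8% in the two decaying scenarios above. Use the same structure for the secondary outcomes.

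The cost is a sentence or two and more computing in R, with no new data or participants. The downside is a somewhat wider confidence interval and some loss of nominal power.

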### Participant eligibility and recruitment

During the 28-month data collection period, in the hospitals conducting this risk prediction intervention, it is intended that all pregnant women with singleton pregnancy who attend prenatal visit before 13^+6^ gestational weeks will be inquire to participate this study. Those women signing the informed consent will receive the Bayes-theorem based preeclampsia risk prediction.

The inclusion criteria are: maternal age ≥ 18 years old, singleton pregnancy, and prenatal visit between 11–13^+6^ weeks of gestational age, and agreement to the informed consent. The exclusion criteria were: multiple pregnancy, first prenatal visit after 14 weeks of gestational age, with severe fetal abnormalities, regular taking aspirin before first antenatal visit, complicated with severe psychological diseases or other diseases which are inappropriate for the study. All enrolled women have the chance to decline participating in or opting out during followup period.

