### Risk assessment

The implementation of the Bayes-theorem based preeclampsia risk prediction will be calculated by the model of The Fetal Maternal Foundation (https://fetalmedicine.org/research/assess/preeclampsia/first-trimester). This model is derived from maternal history, MAP, UTPI and serum PlGF at 11–13^+6^ weeks. Maternal history includes age, race, height, weight, gestational week based on crown rump length (CRL), pregnancy history, use of artificial reproductive technique, smoking history, history of chronic diseases (hypertension, diabetes mellitus, renal disease), adverse pregnancy history, previous history of preeclampsia, history of autoimmune diseases, pregnancy interval over 10 years, systolic blood pressure ≥ 130mmH and (or) diastolic blood pressure ≥ 80 mmHg, obstructive sleep apnea syndrome and previous history of prenatal diagnosis such as villus biopsy and amniocentesis.

The results of laboratory examination will be collected, including levels of folic acid, vitamin B12, fasting blood glucose, blood routine, urine routine, renal function, liver function, blood lipid and coagulation function. Blood pressure is measured by validated automated devices (OMRON, HBP-1320, China) according to a standardized protocol.

Uterine artery PI (UTPI) is measured by Doppler examination of uterine arteries technique in the period from 11 to 13^+6^ gestational weeks. Since this is a common time for first-trimester ultrasound examination in mainland China, UTPI measurement in this trial is practical and available. For the first-trimester transabdominal assessment of uterine artery resistance, a midsagittal section of the uterus and cervix is obtained initially. Using color flow mapping, the transducer is gently tilted sideways, in the purpose that the uterine arteries are identified with high-velocity blood flow along the side of the cervix and uterus. The pulsed-wave Doppler sampling gate should be narrow (set at approximately 2 mm) and positioned on either the ascending or descending branch of the uterine artery at the point closest to the internal cervical os, with an insonation angle < 30◦. In order to verify that the uterine artery is being examined, the peak systolic velocity should be > 60 cm/s. The PI is measured when at least three identical wave forms are obtained. Detailed methodology can be referred to the guideline and published papers [19, 20].

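### The outcome models and a prespecified subgroup use the estimated screening risk, which the protocol gives no way to obtain for control-phase women

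*Protocol article*

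**What the plan says.** All references are to the protocol article.

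- **Statistical analysis** sets a logistic mixed model for the primary and secondary outcomes, with "adjustment for the effect of the estimated risk of preeclampsia at screening" and for center. It also prespecifies "subgroups that were categorized according to the estimated risk of preterm preeclampsia and history of preeclampsia".
- **Risk assessment** defines one risk estimate, the Fetal Medicine Foundation score: "This model is derived from maternal history, MAP, UTPI and serum PlGF at 11–13^+6^ weeks". No version without PlGF is given.
- **Potential for contamination** states: "As PlGF measurement is not available in all eighteen sectors till the initiation of intervention". It concludes that the "preeclampsia risk preventive strategy will not be accessible to clinicians during the baseline phase".
- **Participant eligibility and recruitment** describes women being approached in hospitals that are conducting the intervention, and adds: "Those women signing the informed consent will receive the Bayes-theorem based preeclampsia risk prediction".
- **Traditional preeclampsia prevention** gives control-phase women usual care, which is expected to vary between services and clinicians.
- **Study design and setting** takes the trial result from a comparison of the baseline periods with the follow-up periods, all hospitals combined.

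**The concern.** In this trial the screening is the intervention. A variable produced by the screening exists, as the data collection is described, only for women seen after their hospital has crossed over. Putting it in a model meant to compare women before and after crossover asks for a value that half of the comparison does not have.

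Two analyses are affected. One is the model for the primary and secondary outcomes, from which the main odds ratio is to come. The other is the prespecified subgroup analysis by estimated risk. That analysis covers the women at or above the 1/100 cut-off, who are the only women to whom the strategy assigns aspirin, so it is where a reader would look first for an effect.

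**Working it through.** **The protocol's own figure.** The Sample size section expects 15,000 registrations and 70% participation: 15,000 × 0.70 = 10,500, as stated. This is a recruitment forecast. No event rate, effect size or intracluster correlation is given, so no power consequence can be computed. The question here is whether the effect can be estimated at all.

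**Notation.** For woman i, let A = 1 in the intervention phase and 0 in the control phase, and let R be the estimated risk at screening. The fixed part of the model is an intercept, A, R and 17 indicators for 18 centers, that is 1 + 1 + 1 + 17 = 20 columns. As the data collection is described, R is observed only when A = 1.

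**Check by matrix rank.** Fig. 1 is not shown, so the layout is assumed: 18 hospitals, 28 monthly periods, two-month steps after two baseline months, equal recruitment, and 6, 9 or 12 sequences.

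| Handling of R | Columns | Rank | Reason |
|---|---|---|---|
| Complete cases | 20 | 19 | Every remaining woman has A = 1, so A equals the intercept |
| Missing-indicator M added | 21 | 20 | M = 1 − A, so A + M equals the intercept |
| R known for all women | 20 | 20 | All terms estimable |

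The results were the same for 6, 9 and 12 sequences. They do not depend on the layout, because they follow from A = 1 among complete cases and from M = 1 − A. Treating center as random, or adding calendar-period terms, leaves both identities in place.

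**Subgroups.** Membership of a stratum of R requires R to be observed, so each stratum holds women with A = 1 only and has no between-phase contrast. The other prespecified subgroup, history of preeclampsia, does not need PlGF and can be formed in both phases if that history is recorded.

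**Share of women affected.** Under the assumed 28-month layouts the mean control time per hospital is 7, 10 or 11 months, giving 7/28 = 25%, 10/28 = 36% and 11/28 = 39%. If only the 18-month enrollment period is counted, there are 18 × 18 = 324 hospital-months. Of these, 126 to 180 are control time under other assumed rollouts, giving 126/324 = 39% to 180/324 = 56%. The range of 25% to 56% reflects the assumptions and is not an estimate from the protocol. The rank result does not use it.

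**The case against.** The best reply is that the protocol does not strictly say the risk can never be calculated for control-phase women.

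- The contamination paragraph concerns what clinicians can use, not what researchers may work out later.
- Samples are stored at −80 ℃, so a later assay is possible in principle.
- Process evaluation invites women attending early without confining this to intervention hospitals.
- The blinding section speaks of participants who know the stage their service is in.
- Study design and setting promises baseline data without listing the items.
- The phrase about PlGF in all eighteen sectors could mean that some sectors have it.
- The analysis section does not repeat that the risk is the four-marker one.

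What stands is that the wording should be that the protocol describes no route to this covariate in the control phase, not that none could exist. The rest does not remove the conflict. The sentence on PlGF itself concludes that the strategy is out of reach during baseline. Recruitment and risk assessment are tied to intervention hospitals. No section describes control-phase sampling, and no other score is defined.

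It may also be said that missing-data handling belongs in the statistical analysis plan. That is generally fair, and the protocol does not specify a complete-case fit. But the article names the covariate and the subgroup, and any analysis plan would have to redefine or remove them.

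A reader might go further and infer that no workaround is legitimate. The documents do not support that: control-phase samples assayed later, or a score computed the same way in both phases, would give a proper covariate.

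**Conclusion.** The point holds as a conflict between the stated analysis and the protocol's own data collection. As described, the covariate and the risk-subgroup variable are unavailable for 100% of control-phase women. Under that condition the intervention effect is not identified with complete cases (rank 19 of 20) or with a missing-indicator (rank 20 of 21), and the risk subgroups have no controls. This rests on two readings: that the estimated risk in the analysis section is the four-marker score, the only one defined, and that no control-phase PlGF is collected, since none is described.

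A reader might infer that the primary comparison is lost. It is not: with the covariate defined in both phases, or dropped, the phase effect is estimable. Nor can the size be put as a firm percentage of the sample. Fig. 1 is not shown, and the 10,500 may count only consenting women in intervention hospitals. The correction is still needed before analysis, because the model as written cannot deliver the main estimate.

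**What to change.** In the between-phase models and the subgroup analysis, do one of the following:

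1. Replace the four-marker risk with baseline items obtained identically in both phases, for example age, body mass index, parity, previous preeclampsia, chronic hypertension, diabetes, renal or autoimmune disease, assisted conception and booking blood pressure. A single maternal-history-only score would also serve. Define the risk subgroup from the same variables.
2. Remove the estimated risk as a covariate and drop the risk subgroup from the between-phase comparison.

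Under either option, keep the four-marker risk for description within the intervention phase.

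Before choosing the first option, confirm that the items can be extracted for control-phase women in all eighteen hospitals. The protocol describes electronic records as the source for outcomes but does not say that booking variables will be available from them. The cost is a change of wording, some extra record extraction, and a covariate that is probably less prognostic than the four-marker risk. The second option needs only the change of wording, but gives up the adjustment and the risk-subgroup comparison.
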